##### Sustainment

We expect that the moderating effect of leadership [66] will hold true for A-CRA sustainment. We also expect changes in external support [65] during the sustainment period to function as a mediator variable, because state-focused grants might influence the availability of funding. Furthermore, we anticipate additional moderators and mediators based on the eight domains of EBP sustainment capacity identified in the Public Health Sustainability Framework [50]. We will measure these domains with the 40-item Program Sustainability Assessment Tool [67]; ratings use a seven-point scale (0=“to little or no extent,” 7=“to a very great extent”) and are averaged to produce an overall sustainment capacity score and domain subscale scores. We expect that differences in sustainment between state-focused and organization-focused grants will be mediated by increases in the “funding stability” domain over time and moderated by overall sustainment capacity.

#### Descriptive measures of A-CRA barriers and facilitators

We will collect various other measures that characterize the states and organizations implementing A-CRA. Broadly, the measures align with our previous project while capturing important constructs from all major EPIS domains: innovation, inner context, outer context, and bridging factors that link outer and inner contexts. The measures include both structured, closed-response questions and open-ended exploration of barriers and facilitators. We briefly describe specific topics asked about here; for details, see Additional files 2 and 3.

*Innovation factor* measures capture participants’ perceptions of and attitudes toward the A-CRA model (e.g., complexity, relative advantage). *Inner context* measures describe the treatment organizations delivering A-CRA, including their focus of services, staffing (e.g., number of therapists and supervisors, turnover rates), adolescent SUD treatment capacity (e.g., number of youth served, length of stay), and organizational plans to spread and sustain A-CRA (or not). Sustainment capacities captured by the Program Sustainability Assessment Tool [67] will also be considered here, as will a recently published measure of the organization’s financial climate [82]. *Outer context* measures describe extra-organizational factors, including sources of adolescent SUD treatment referrals, formal partnerships between organizations, and policies that affected A-CRA penetration and sustainment. The inclusion of state agency administrators’ views will greatly expand our understanding of outer context factors. Finally, we will collect detailed descriptions of *bridging factors* by asking state agency administrators about A-CRA infrastructure developed in their state. These questions will explore how each state tailored [83–85] their grant-funded efforts to local contexts and allow us to examine if certain infrastructure components were associated with A-CRA penetration and sustainment.

#### COVID-19 impact

Our project timeline coincides with the COVID-19 pandemic, so we must consider the potential impacts on key project outcomes. Actions to prevent the spread of COVID-19, such as telehealth service delivery [86, 87], and budget shortfalls due to economic constriction [88] are transforming U.S. behavioral health services [89]. We expect statistical controls or corrections (i.e., sensitivity analyses) will likely be insufficient to account for the far-reaching and inter-related impacts of the pandemic on employment, treatment availability, substance use, and funding priorities [90]. Instead, we will gather mixed-method data to help us understand the contextual influences of COVID-19 on A-CRA penetration and sustainment. In Wave 1 interviews, we will ask how the COVID-19 pandemic has impacted A-CRA services, barriers to penetration and sustainment, and strategies used to address those barriers. The Wave 1 survey will include additional items about how COVID-19 impacted A-CRA services. These questions may be repeated or modified in later waves, depending on the course of the pandemic.

#### Measures for sensitivity analyses

To help understand trends that may be confounded with grant type in our quasi-experimental design, we will conduct a series of sensitivity analyses. We will account for non-secular trends by creating a series of binary variables (using CHS records) that indicate which years each state had active SAMHSA state-focused grant support. To account for secular trends, we will collect non-equivalent dependent variables [91, 92] from publicly available data about the participating treatment organizations. Non-equivalent dependent variables are uniquely useful when comparing groups exposed to different policy interventions in non-overlapping time periods with no control groups available. These variables capture an observed secular trend because they (1) *are not* expected to be influenced by the predictor variable of interest (i.e., grant type) but (2) *are* expected to be influenced by factors that provide an alternate explanation for observed differences (i.e., other factors that could promote EBP implementation at SUD treatment organizations).

The non-equivalent dependent variable design is strengthened by the inclusion of multiple variables, each with controlled covariates. At a minimum, we plan to examine variables representing organization-level use of medication treatments for opioid use disorder (e.g., methadone detoxification/maintenance, buprenorphine use) as non-equivalent dependent variables; each represents a discrete EBP that could be influenced (as with A-CRA) by efforts to improve substance use care, but not by A-CRA-focused grants. We will collect each variable from the publicly available National Survey of Substance Abuse Treatment Services (N-SSATS) [93], an annual census of SUD treatment organizations (since 2000; response rates ≥90%), and control for increases in state-level (a) opioid-related overdose death rates among adults using CDC cause of death data [94] and (b) SAMHSA grant funding amounts for opioid-specific treatment services [95]. We will also continue exploring N-SSATS data to identify other candidate non-equivalent dependent variables, each of which would require its own set of covariates. We will collect all variables for every year relevant to our analyses; i.e., 2009 (when the first organization-focused grants ended) through 2025 (our final year of data collection).

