### Project context

As noted earlier, SAMHSA has used both organization-focused and state-focused discretionary grant strategies to fund EBP implementation (including A-CRA) for adolescent SUD. All grants were administered by SAMHSA’s Center for Substance Abuse Treatment [59], whose primary role was to provide funding, oversight, and national leadership to grantee organizations and states/territories/tribal entities (hereafter, “states”). SAMHSA funded (i) four cohorts of organization-focused grantees, awarded 2006–2010, across 26 states followed by (ii) four cohorts of state-focused grantees, awarded 2012–2017, across 22 states. Eight states had recipients of both grant mechanisms, so overall, 40 states were represented across cohorts.

In both initiatives, SAMHSA partnered with Chestnut Health Systems (CHS; an organization that conducts A-CRA training and research) to provide training and certification for A-CRA clinicians and supervisors. CHS provided a standardized, 2.5-day training for all organization-focused grantees and most clinicians in state-focused grantees’ states—although some received training from certified A-CRA supervisors. In every case, CHS still oversaw A-CRA clinician and supervisor certification. Certification activities required each trainee to demonstrate competency in delivering A-CRA treatment and/or supervision procedures, depending on their role. Specifically, clinicians and supervisors participated in twice monthly, group-format coaching calls with CHS expert consultants; they also submitted audio-recorded A-CRA therapy or supervision sessions, respectively, and their consultant provided numeric ratings and written feedback [60–62]. Typically, the certification process lasted from 6 months to a year.

Next, we describe the two grant types in more detail. We follow recommendations for specifying implementation strategies in terms of actors, actions, action targets, temporality, dose, outcomes, and justification [27, 36].

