#### Organization-focused grants

SAMHSA awarded these grants directly to treatment organizations. Grantees received ~$900,000 across a 3-year period to support A-CRA implementation. These grants targeted the EPIS inner context by paying for clinicians delivering A-CRA, supervisors providing A-CRA supervision, and related activities such as evaluation (see https://externallinks.samhsa.gov/grants/2009/ti_09_002.dhtml to view a representative request for proposals). Our prior work showed that grantees generally had initial success in implementing A-CRA with fidelity and reducing youth substance use, but many did not sustain A-CRA post-funding [32–34].

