##### Penetration

We define penetration as the proportion of providers (i.e., clinicians and supervisors) in a service system that were certified in A-CRA during active implementation. We will use CHS administrative records to define and measure penetration (see Table 2). Potential providers (i.e., the denominator) will include all individuals eligible for training and/or certification activities at a treatment organization during the state-focused grant period; the grant funding period will be treated as active implementation. Certification status will be based on CHS’s standard definitions for different levels and types of A-CRA certification.

A-CRA clinician certification is based on proficient demonstration of A-CRA procedures, which are 19 clinical techniques or activities used by clinicians (e.g., functional analysis of substance use, problem-solving, communication skills); first-level certification indicates proficiency in nine basic procedures, and full certification indicates proficiency in every procedure [13]. Further certification for proficiency with transition-age youth (ages 18–25) is also available and considers two additional procedures. A-CRA supervisor certification is based on proficient demonstration of supervision-specific skills and knowledge, as well as the ability to accurately and reliably rate A-CRA sessions. We will construct several penetration variables, representing the percent of participants achieving any certification as well as first-level, full, transition-age youth, or supervisor certifications.

We will also verify that each certified individual achieved adequate A-CRA fidelity, defined as an average competence rating of ≥3 out of 5 across the relevant activities for a given A-CRA certification (i.e., procedures in session recordings, supervisors’ competence in rating sessions) following past research [14, 16, 17]. We will calculate average fidelity scores that contributed to each individual’s clinical (first-level, full, transition-age) and/or supervisor certification; the same ratings can contribute to all clinical certifications, so these cannot be calculated separately. We will also calculate descriptive measures for each certification type characterizing time to certification, number of session recordings reviewed, and procedure-specific scores.

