### Analysis plan

Our analytic approach is grounded in mixed methods [57], combining quantitative data (standardized interview and survey items) and qualitative data (e.g., open-ended interview questions, document review, focus groups) to gain higher-level insights beyond what either approach provides in isolation. Qualitative data will deepen our understanding of quantitative findings in aims 1 and 2, representing a QUAN + Qual mixed-method design; we will rely more heavily on the qualitative data for aim 3, taking a QUAL + Quan approach [57].

Aim 1 only requires CHS administrative data, qualitative data collected in year 1, and non-equivalent dependent variables, so we plan to complete data analysis by the end of year 2. For aim 2, we will conduct waves of data collection across 4 years (see Table 1), maintaining progress on data management, document review, and non-equivalent dependent variable collection during low-effort recruitment periods. Aim 3 will use data from the main waves, which we will separate and incorporate into comparative case studies in years 4 and 5—along with the focus group data.

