#### Sensitivity analyses

Sensitivity analyses will account for observed and unobserved secular trends, using the same models for penetration and sustainment. First, we will test non-equivalent-dependent variables (medication treatment variables) as *Y*^*N*^ outcomes, moderators during the grant funding period (aim 1a) or in each year of sustainment (aim 2a). We hypothesize grant type will not have significant effects on non-equivalent dependent variables, but if we find one, we will adjust the standardized effect size for the relevant outcome (penetration or sustainment) by subtracting out the effect size for the non-equivalent dependent variable. Second, we will repeat all primary analyses controlling for each organizations’ years of active funding (time fixed efforts), which could capture unobserved secular trends missed by our non-equivalent-dependent variables. If grant effects are reduced by controlling for time, we will use our qualitative data to help understand why.

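### The 2009 start for the non-equivalent dependent variables omits 2006–2008, funding years of the earliest organization-focused grants that the Aim 1 sensitivity analysis calls for

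*Protocol article*

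**What the plan says.** The Measures for sensitivity analyses section gives the window in explicit years: "We will collect all variables for every year relevant to our analyses; i.e., 2009 (when the first organization-focused grants ended) through 2025". The variables are organization-level measures of medication treatment for opioid use disorder, taken from a national survey described as an annual census ("since 2000; response rates ≥90" percent). The covariates are state-level opioid overdose deaths and federal opioid-treatment grant funding.

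The Sensitivity analyses section then puts these variables in place of the outcome, "moderators during the grant funding period (aim 1a) or in each year of sustainment (aim 2a"). If grant type shows an effect on one of them, its standardized effect size is subtracted from that of penetration or sustainment.

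The funding periods come from three places. Project context lists "four cohorts of organization-focused grantees, awarded 2006–2010, across 26 states" and "four cohorts of state-focused grantees, awarded 2012–2017, across 22 states". Organization-focused grants adds: "Grantees received ~$900,000 across a 3-year period to support A-CRA implementation". For the penetration outcome, "the grant funding period will be treated as active implementation".

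The Analysis plan confirms that Aim 1 depends on these variables: "Aim 1 only requires CHS administrative data, qualitative data collected in year 1, and non-equivalent dependent variables".

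**The concern.** The window opens in the year the first organization-focused grants closed. That is the right opening for a post-funding analysis and the wrong one for an analysis of the funding period. The article calls the window complete, yet it leaves out years in which the comparator grants were active.

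The omission is one-sided. The two grant types ran in largely separate calendar periods, and the non-equivalent dependent variables are there to measure how far background change between those periods could account for a difference in outcome. Cutting the early years from one arm only can distort that measurement. The result may also feed into an adjusted effect size for penetration, so the consequence need not stop at a descriptive check.

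**Working it through.** **Inputs.** Collection window 2009–2025 (Measures for sensitivity analyses). Four organization-focused cohorts awarded 2006–2010 (Project context), 3 years each (Organization-focused grants). State-focused awards from 2012, with eligible cohorts running 2013–2017, 2012–2018 and 2017–2021 (Project context; Table 1).

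**The protocol's own figure.** First award year plus grant length: 2006 + 3 = 2009. This reproduces the stated end of the first organization-focused grants, so the three sections agree on dates.

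**Funding years before 2009, by award year.** Years can be counted in two ways: as three 12-month grant-years labelled by start year, or as the four calendar years from award to end.

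| Award year | Grant-years by start year | Lost | Calendar years touched | Lost |
|---|---|---|---|---|
| 2006 | 2006–2008 | 3 of 3 | 2006–2009 | 3 of 4 |
| 2007 | 2007–2009 | 2 of 3 | 2007–2010 | 2 of 4 |
| 2008 | 2008–2010 | 1 of 3 | 2008–2011 | 1 of 4 |
| 2009 | 2009–2011 | 0 of 3 | 2009–2012 | 0 of 4 |
| 2010 | 2010–2012 | 0 of 3 | 2010–2013 | 0 of 4 |

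**Totals over four cohorts.** The first and last award years are 2006 and 2010; the middle two are not stated. The denominators are 4 × 3 = 12 grant-years, or 4 × 4 = 16 calendar years touched.

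- Awards 2006, 2007, 2008, 2010: 3 + 2 + 1 + 0 = 6 lost
- Awards 2006, 2007, 2009, 2010: 3 + 2 + 0 + 0 = 5 lost
- Awards 2006, 2008, 2009, 2010: 3 + 1 + 0 + 0 = 4 lost
- Awards 2006, 2009, 2009, 2010 (two cohorts sharing a year): 3 + 0 + 0 + 0 = 3 lost

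This gives 3–6 of 12 (25–50%) by start year, or 3–6 of 16 (19–38%) by calendar years touched. With distinct award years the range is 4–6. The lower end of 3 is the loss from the 2006 cohort alone. The upper end of 6 assumes that no two cohorts share an early award year. Cohorts are not weighted by size.

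**Overall span.** Organization-focused funding touches 2006–2013, which is 8 calendar years, of which 3 fall before the window. State-focused funding in Table 1 spans 2012–2021, of which none do.

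**After the change.** 2006–2025 is 2025 − 2006 + 1 = 20 calendar years, against 2025 − 2009 + 1 = 17 now. The three added years cover every organization-focused funding year.

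**The case against.** The strongest reply is that Aim 1 is a snapshot. The abstract's Method paragraph places penetration at the end of grant funding, and 2009 is the first year in which such a value exists. The Sensitivity analyses section asks for every year only under Aim 2a, and the Quantitative data analysis section reserves repeated measurements for Aim 2. One value per organization might be enough for Aim 1a, and the year indexing may be in Additional file 4, which is not shown.

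This softens the point without removing it. The Sensitivity analyses section refers to the funding period, the Penetration section treats that whole period as active implementation, and the A-CRA certification records section counts certification achieved during it. The window is also not left open for another document: it is stated in years and described as complete. If a snapshot is meant, the Sensitivity analyses wording needs correcting instead.

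A reader might infer more than the documents support:

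- *That the 2006 cohort has no usable data.* Its grants ended in 2009, so that calendar year remains; it loses every year only if grant-years are labelled by start year.
- *That the main penetration result is compromised.* That outcome comes from certification records and does not use these variables.
- *That the bias has a known direction and size.* The protocol gives no trend for medication treatment, the models adjust for overdose deaths and opioid funding, and subtraction occurs only if a grant-type effect is found. A second planned check, controlling for years of active funding, does not rest on these variables.

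**Conclusion.** The stated window and the stated Aim 1a analysis do not fit together. Taken as written, calendar years 2006–2008 are missing for the earliest organization-focused cohort or cohorts and for no state-focused cohort. The proportion lost depends on unstated award years and on how years are labelled, so it can be given only as the ranges above. Cohorts awarded in 2009 or 2010 are fully covered.

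The consequence is limited to one of the two planned secular-trend checks for Aim 1 and to the conditional adjustment drawn from it. If medication treatment rose over calendar time after covariate adjustment (an assumption the documents neither support nor contradict), dropping the early years would raise the organization-focused level and understate the gap between arms. Too little would then be subtracted, or nothing if the effect went undetected, and the adjusted state-focused advantage would be too large. A falling trend would reverse this. The point deserves correction because the design is not randomized, the arms are separated in time, and the change is small.

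**What to change.** Start collection of the non-equivalent dependent variables and their covariates in 2006, and state that Aim 1a uses each organization's own funding years and Aim 2a its post-funding years. A 2005 value is optional: it helps only if the covariate increases are computed year on year, and no stated analysis requires a pre-award year.

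If only end-of-grant values are intended for Aim 1a, keep 2009 and reword the Sensitivity analyses section to say so.

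The cost is three more calendar years of data to obtain and link, with no new participants. The protocol says the treatment survey has run annually since 2000. It gives no start year for the overdose-death or grant-funding sources, so their availability for 2006–2008 should be confirmed. The change should come early, because the Analysis plan has Aim 1 analysis finished by the end of year 2.

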#### Policy implications

For aim 3, we will explore government agencies’ adoption of financing strategies rather than treatment organizations’ adoption of A-CRA. We will develop focus group facilitation guides based on a recent adaptation [96] of the Consolidated Framework for Implementation Research (CFIR [97, 98]) for policy implementation. Questions will be tailored to the characteristics of attendees, soliciting views about the use of organization-focused versus state-focused grants to support EBP penetration and sustainment; usefulness of states’ and organizations’ grant-funded activities; and barriers and facilitators for high-priority changes—related to characteristics of policy changes, policymakers, inner-context government agencies, and outer-context public opinion and political climates. Focus group discussions will be guided by our findings from aims 1 and 2.

### Analysis plan

Our analytic approach is grounded in mixed methods [57], combining quantitative data (standardized interview and survey items) and qualitative data (e.g., open-ended interview questions, document review, focus groups) to gain higher-level insights beyond what either approach provides in isolation. Qualitative data will deepen our understanding of quantitative findings in aims 1 and 2, representing a QUAN + Qual mixed-method design; we will rely more heavily on the qualitative data for aim 3, taking a QUAL + Quan approach [57].

Aim 1 only requires CHS administrative data, qualitative data collected in year 1, and non-equivalent dependent variables, so we plan to complete data analysis by the end of year 2. For aim 2, we will conduct waves of data collection across 4 years (see Table 1), maintaining progress on data management, document review, and non-equivalent dependent variable collection during low-effort recruitment periods. Aim 3 will use data from the main waves, which we will separate and incorporate into comparative case studies in years 4 and 5—along with the focus group data.

